## Abstract

**Objectives::**

The purpose of this study is to analyze and compare the effectiveness, economic feasibility, and safety of using an integrated medical service critical pathway (CP) in L-HNP patients.

**Methods::**

This single-center prospective observational study will be performed at Kyung Hee University Medicine Hospital and Kyung Hee University Korean Medicine Hospital. The inclusion criteria are a diagnosis of L-HNP on magnetic resonance imaging or computed tomography scans, age under 80 years, a visual analog scale score of 7 or higher for either lower back pain or lower extremity pain. The included 102 participants will be classified into 6 groups (n = 17 in each group): CP application with conservative treatment; CP application with open discectomy; CP application with intrabody fusion; conservative treatment without CP application; open discectomy without CP application; and interbody fusion without CP application. We will collect data on the visual analog scale, ODI, SF-36, and EQ-5D-3L scores; number of admission days; medical staff satisfaction; patients health service satisfaction; waiting time for consultations; use of pain relievers; and CP application and completion rates.

**Conclusion::**

In future, this study is expected to serve as a basis for follow-up studies on the development and application of CPs in integrated medical services for various diseases, including lumbar herniated nucleus pulposus.

## 1. Introduction

Lumbar herniated nucleus pulposus (L-HNP) is a condition in which fibroblasts undergo degenerative changes or external forces in the intervertebral disc and a part of the nucleus escapes, causing neurological symptoms due to compression of the dura mater or nerve root.^[1]^ According to a study by the Health Insurance Review and Assessment Service in 2021, intervertebral disc disorder is the 4th largest medical inpatient disease and 9th largest contributor to Western medical expenses and the 4th largest medical inpatient disease and 3rd largest contributor to Korean medical expenses in Korean.^[2]^ In Western medicine (WM), L-HNP treatment is divided into conservative and surgical treatments. Lumbar surgery, which mainly consists of open discectomy and interbody fusion, is usually performed when conservative treatments, such as epidural blocking and facet joint blocking, are ineffective.^[3]^ In Korean medicine (KM), conservative treatment is chiefly performed and includes thermotherapy, herbal medicine, Chuna therapy, acupuncture-moxibustion therapy, and pharmaco-acupuncture therapy.^[4]^

Currently, Korea’s medical system is a dual system that separates WM and KM; however, the revision of medical laws in 2009 allowed WM doctors to cooperate with KM doctors at the hospital level. The Ministry of Health and Welfare started a Western-Korean medicine collaborative pilot project in 2016, and Step 4 of the project has been in progress since April 15, 2022.^[5]^ At the same time, the number of patients seeking integrated medical services not officially included in the existing medical system, such as diet and dance therapy, is increasing due to improved living standards, increased health interest, and increases prevalence of chronic incurable diseases.^[6]^

In addition to the existing cooperation system between WM and KM, integrated medical services provide comprehensive medical services to patients through complementary and alternative medicine (CAM), the safety and effectiveness of which have been verified in areas where conventional medicine has limitations (mainly mental, spiritual, and social health).^[7]^ Recently, the Ministry of Health and Welfare conducted an integrated medical research support project to prepare a model of integrated medical care, a new medical paradigm in which WM and KM doctors develop integrated diagnosis and treatment technologies with equal qualifications, encompassing various complementary and alternative medicine techniques.^[8]^

The critical pathway (CP) is a tool that lists the interventions of doctors, nurses, and other medical personnel over time to standardize the contents of medical interventions to be applied and maximize efficiency while minimizing medical costs within a fixed hospitalization period.^[9–11]^ After CP was first applied in the medical environment in the United States in the 1990s, it has been applied in clinical settings in Korea since the late 1990s. Recently, there has been a growing movement to introduce and apply CP in the clinical field of KM to improve the quality of medical care and patient satisfaction with medical services.

To date, CP has been studied in WM^[12,13]^ and KM^[14]^ for L-HNP, a commonly encountered disease in both WM and KM contributing to the economic burden. Although there have been studies on CP based on collaboration between WM and KM for patients with acute pain after lumbar spine surgery,^[15]^ there have been no studies on an integrated medical service CP.

An integrated medical service CP encompassing WM, KM, and CAM for L-HNP has been developed at the Department of Neurosurgery and Korean Rehabilitation Medicine at Kyung Hee Medical Center. However, further research is necessary before its clinical application.

In this study, patients with L-HNP were divided into groups that received integrated medical service CP and those that did not. They were prospectively observed to analyze and compare the effectiveness, economic feasibility, and safety of the CP.

## 2. Materials and methods

### 2.1. Study design

This single-center prospective observational study will be performed at Kyung Hee University Medicine Hospital and Kyung Hee University Korean Medicine Hospital to analyze the effectiveness, economy, and safety of using an integrated medical service CP in patients with L-HNP. The patients will be divided into groups that apply critical pathway of integrative medical services and those who do not.

From among the patients who agree to participate in the study, those who meet the inclusion criteria will be registered as research subjects. Among them, those who agree to participate in the integrated medical service CP will be assigned to the test group (integrated medical service CP applied group) and those who do not will be assigned to the control group (integrated medical service CP non-applied group). Both groups are further divided into a conservative treatment (CONS) group, an open discectomy (DISCEC) group, and an interbody fusion (FUSION) group based on the main medical treatment. In the test group, inpatient treatment will be administered according to the pathway of the prescribed protocol. In the control group, inpatient treatment will be administered based on the treating doctor’s judgment, without a prescribed pathway. The test group patients will be discharged after being hospitalized for a set hospitalization date, whereas in the control group, the time of discharge will be determined according to the judgment of the clinician. The study will be completed when the patients are evaluated during an outpatient visit to the Department of Neurosurgery of Kyung Hee Medical Center 4 weeks after discharge.

### 2.2. Study registration

The trial protocol was approved by the Institutional Review Board of Kyung Hee University Korean Medicine Hospital in July, 2022 (KHUH-2022-06-024-002).

This protocol was registered with the Clinical Research Information Service (CRIS) on 02 Sep 2022 (KCT0007671; https://cris.nih.go.kr/cris/search/detailSearch.do?seq=22923&search_page=L).

### 2.3. Participants

Patients with L-HNP visiting the Neurosurgery outpatient department of Kyung Hee Medical Center judged to need inpatient treatment will be guided to this study. Doctors and research nurses will select/exclude these patients after obtaining informed consent from those who express their intention to participate in the study. The doctors and research nurses will evaluate whether the patients meet the inclusion/exclusion criteria and enroll patients deemed suitable for this study. Depending on their intention to participate in the integrated medical service CP application, participants will be assigned to the test and control groups.

#### 2.3.1. Inclusion criteria

(1).Diagnosis of L-HNP through magnetic resonance imaging or computed tomography.(2).Ages <80 years.(3).Complaint of both lower back pain and lower extremity pain at the same time.(4).Visual analog scale (VAS) score of 7 or higher for either lower back pain or lower extremity pain.(5).Voluntary agreement to participate in this study.

#### 2.3.2. Exclusion criteria

(1).Suspected malignant tumor, spinal infection, or osteoporotic compression fracture.(2).Need of immediate surgery due to another disease.(3).Serious underlying disease.(4).More pain due to musculoskeletal disease than due to L-HNP.(5).Medical benefits, Auto insurance.(6).Other patients whom the investigator deems unsuitable to apply CP in this clinical trial.

### 2.4. Clinical trial plan and critical pathway schedule

Among patients with lumbar intervertebral disc herniation visiting the Neurosurgery outpatient department of Kyung Hee Medical Center, patients with a VAS score of 7 or higher who require hospitalization can consent to participate in this study. Following patient consent, the doctors and research nurses will screen the patients according to the inclusion and exclusion criteria, enroll those who pass the screening, and confirm the participants intention to receive treatment using an integrated medical service CP. Depending on their intention to participate in the CP application, participants will be classified into the test or control group. Upon admission, the patients will be assigned to the CONS group, DISCEC group, and FUSION groups according to the judgment of the medical staff. The test group will receive inpatient treatment according to a previously developed integrated medical service CP plan, and the control group will receive inpatient treatment according to the clinician’s judgment without a set protocol. The study will be deemed complete when all patients will be evaluated during an outpatient visit to the Neurosurgery Department of Kyung Hee Medical Center 4 weeks after discharge.

#### 2.4.1. CP applied group

The CP-CONS group will follow the treatment schedule presented in Figure 1, the CP-DISCEC group will follow the treatment schedule shown in Figure 2, and the CP-FUSION group will follow the treatment schedule shown in Figure 3.

**Figure 1. F1:**
[figure not shown]
Critical pathway – conservative treatment group (CP-CONS group). CONS = conservative treatment, CP = critical pathway.

**Figure 2. F2:**
[figure not shown]
Critical pathway – open discectomy group (CP-DISCEC group). CP = critical pathway, DISCEC = open discectomy.

**Figure 3. F3:**
[figure not shown]
Critical pathway – interbody fusion group (CP-FUSION group). CP = critical pathway, FUSION = interbody fusion.

#### 2.4.2. CP non-applied group

According to the medical treatment method, the patients will be classified into the control-CONS group, control-DISCEC group, and control-FUSION group. In addition to WM treatment, KM treatment, such as acupuncture, moxibustion, cupping treatment, Chuna therapy, and herbal medicine treatment may be administered as necessary.

### 2.5. Sample size

A previous study^[16]^ evaluated the clinical effect of warm acupuncture on patients with lumbar disc herniation. The treatment group received warm acupuncture, the control group received traction treatment, and both groups were treated twice. The mean and standard deviation (mean ± SD) of the patients VAS scores before and after treatment are shown in the table 1.

**Table 1 T1:** The mean and standard deviation (mean ± SD) of the patients visual analogue scale scores before and after treatment.

	Subjects	Before treatment (B)	After treatment (A)
Treatment group	45	6.14 ± 1.29	2.27 ± 0.84
Control group	37	6.09 ± 1.21	3.37 ± 0.93

SD = standard deviation.

#### 2.5.1. Average change in the VAS score

The average change in VAS was calculated as 2.27 to 6.14 = −3.87 in the treatment group and 3.37 to 6.09 = −2.72 in the control group. Therefore, the difference in the change in the VAS score before and after treatment between the 2 groups was d=−3.87 to (−2.72) = −1.15.

#### 2.5.2. Variance in the change in the VAS score

Assuming that the correlation coefficient (ρ) for pre- and posttreatment was 0.5, the variance in the VAS score change before and after treatment for the treatment and control groups was calculated as follows:

Treatment group: Var(A−B)=Var(A)+Var(B)−2ρSD(A)SD(B)$=1.29^{2}+0.84^{2}-2*0.5*1.29*0.84\approx 1.13^{2}$

Control group: Var(A−B)=Var(A)+Var(B)−2ρSD(A)SD(B)$=1.21^{2}+0.93^{2}-2*0.5*1.21*0.93\approx 1.10^{2}$

#### 2.5.3. Pooled variance calculation

The pooled variance was calculated to determine the number of subjects, assuming that the variance of the VAS score change before and after treatment in the treatment and control groups was the same.

$$\begin{array}{l} \sigma^{2}=\frac{\left(45-1\right)\times 1.13^{2}+\left(37-1\right)\times 1.10^{2}}{46+37-2}\approx 1.12^{2} \end{array}$$

#### 2.5.4. Calculation of the number of subjects

Assuming that the significance level (α) is 5% and the test power (1-β) is 80%, the number of subjects in each group is calculated so that the ratio of the 2 groups is 1:1.

$$\begin{array}{l} n=\frac{2\sigma^{2}{\left(Z_{1-\beta }+Z_{1-\frac{\alpha }{2}}\right)}^{2}}{d^{2}}=\frac{2\times 1.12^{2}{\left(Z_{0.8}+Z_{0.975}\right)}^{2}}{{\left(-1.15\right)}^{2}}\approx 15 \end{array}$$

The CP group is divided into the CONS, DISCEC, and FUSION groups, and CP non-applied group is also divided into the corresponding 3 groups. The minimum number of subjects required for this study is 15 per group, with a total of 90; however, considering the dropout rate (10%), a total of 102 subjects (17 per group) will be enrolled.

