### 2.8. Statistical analysis

#### 2.8.1. Efficacy evaluation analysis

##### 2.8.1.1. Primary outcome analysis

The primary outcomes will be analyzed based on the treatment groups. For each group, a normal distribution will be assumed for the difference in the VAS score measured on day 1 of hospitalization and at 4 weeks after discharge, and a *t* test will be performed. The means between the treatment groups (CP and control groups) will be compared. If normality is confirmed through the normality test for the VAS scores, the Mann–Whitney test will be performed.

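### 15 per group is called the minimum for 80% power, but the planned t test has about 77.5% power there and needs 16 evaluable per group

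*Protocol article*

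**What the plan says.** Section 2.5 takes its inputs from a published comparison of warm acupuncture with traction (Table 1).

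- **Difference:** section 2.5.1 derives "the difference in the change in the VAS score before and after treatment between the 2 groups was" -1.15.
- **Standard deviation of the change:** section 2.5.2 proceeds by "Assuming that the correlation coefficient (ρ) for pre- and posttreatment was 0.5" and obtains 1.13 and 1.10 for the two groups. Section 2.5.3 pools these to 1.12, with the denominator printed as 46+37-2.
- **Error rates:** section 2.5.4 uses a 5% level, two-sided because the quantile is Z0.975, and states that "the test power (1-β) is 80" percent.
- **Result:** "The minimum number of subjects required for this study is 15 per group, with a total of 90". The next step is "considering the dropout rate (10%), a total of 102 subjects (17 per group) will be enrolled".

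Section 2.8.1.1 compares the VAS change between the CP and control arms by a t test, separately in the conservative, discectomy and fusion strata. It adds: "If normality is confirmed through the normality test for the VAS scores, the Mann–Whitney test will be performed".

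**The concern.** The sample-size formula treats the standard deviation as known. The planned t test has to estimate it from about 30 patients per stratum. At this size the difference between the two is no longer negligible, and the t test has less power than the formula implies.

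Each stratum is judged by its own test, and 15 is presented as the minimum for the 80% target. If 15 does not reach 80% with the planned test, that statement is wrong for the analysis that will be run. The chance of missing the assumed effect in a stratum is then higher than the 20% the plan accepts.

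**Working it through.** **Inputs, all from the protocol article.** Difference d = 1.15 (2.5.1); SD = 1.12 (2.5.3); two-sided 5% level, 80% power and 1:1 ratio (2.5.4); 10% dropout and 17 enrolled per group (2.5.4); two-sample t test per stratum (2.8.1.1).

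**1. The plan's own figure.** n = 2·SD²·(Z0.8 + Z0.975)² / d² = 2 × 1.2544 × (0.8416 + 1.9600)² / 1.3225 = 14.89, which rounds up to 15. The normal-theory power at 15 is 80.3%. With 10% dropout, 15 / 0.9 = 16.7, which rounds up to 17. The printed sample size follows from the printed formula.

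**2. Power of the planned test.** For n evaluable per group, the t statistic follows a noncentral t distribution with 2n - 2 degrees of freedom and noncentrality (d/SD)·√(n/2). Here d/SD = 1.15/1.12 = 1.027.

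| Evaluable per group | df | Noncentrality | Critical t | t-test power | Normal-formula power |
|---|---|---|---|---|---|
| 15 | 28 | 2.812 | 2.048 | 77.5% | 80.3% |
| 16 | 30 | 2.904 | 2.042 | 80.2% | 82.7% |
| 17 | 32 | 2.994 | 2.037 | 82.7% | 84.9% |

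Sixteen is therefore the smallest number per group that reaches 80%.

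**3. Enrolment and dropout.** On average 17 × 0.9 = 15.3 patients per group remain. Letting each of the 17 drop out independently with probability 10%, and averaging the t-test power over the resulting group sizes, gives 78.1%. If nobody drops out, power is 82.7%.

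**4. Mann-Whitney, conditional.** In 100,000 simulated trials with normally distributed changes and equal SD 1.12, power at 15 per group was 74.0% (exact or continuity-corrected) or 75.5% (uncorrected). At 17 per group it was 80.4%.

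**5. Pooled-variance line.** The numerator is 44 × 1.13² + 36 × 1.10² = 56.18 + 43.56 = 99.74. Table 1 lists 45 and 37 subjects, so the denominator should be 45 + 37 - 2 = 80, and √(99.74/80) = 1.117, which rounds to the stated 1.12. The printed 46 + 37 - 2 = 81 gives √(99.74/81) = 1.110. With SD 1.110 the formula in step 1 gives 14.6, which also rounds up to 15.

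**The case against.** The strongest defence is that nothing was miscalculated. The normal-quantile formula is a standard approximation, it is printed in full, and 15 is its correct result. This stands: the point is a small-sample gap, not an arithmetic error.

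The gap is also small, at one evaluable patient per group. The planned enrolment of 17 would cover it if losses stayed low, and the average shortfall after 10% dropout is about 2 points. This stands too.

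The gap is small beside the uncertainty in the inputs. Keeping Table 1's standard deviations and 15 per group, t-test power is 70.8% at a pre-post correlation of 0.4, 77.6% at 0.5, 81.3% at 0.55 and 85.0% at 0.6. A shift of 0.05 in an assumed correlation would cancel the shortfall. That limits how much weight the figure can bear. It does not make 15 the minimum for 80% under the assumptions the plan chose.

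A reader might go further and put power at about 74%, because section 2.8.1.1 names the Mann-Whitney test. The document does not support that as the headline. The figure holds for normally distributed changes, and such data go to Mann-Whitney only under the literal wording "If normality is confirmed through the normality test for the VAS scores, the Mann–Whitney test will be performed", which looks like a dropped "not". Under the probable intention the test would serve non-normal data. Its power could then be higher or lower, and the document gives no distribution from which to compute it.

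A reader might also take the misprinted denominator as evidence that the sample size is wrong. Step 5 shows that it is not: the stated 1.12 agrees with the correct denominator.

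**Conclusion.** The point holds in a limited form. For the t test that the protocol plans, 15 evaluable patients per group give about 77.5% power and not 80%, so the risk of missing the assumed effect in a stratum is about 22.5% instead of 20%. The minimum for 80% is 16. At the planned enrolment and dropout, average power is about 78%.

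These figures rest on the plan's own d = 1.15, SD = 1.12 (hence correlation 0.5), a two-sided 5% level, normally distributed changes with equal variance and, for the 78%, independent random dropout. The sentence is worth correcting because it is the stated basis for the size of each stratum. The shortfall alone does not call the design into question.

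**What to change.** In section 2.5.4, replace the claim that 15 is the minimum. State that 15 evaluable patients per group give about 77% power for the two-sample t test at the assumed difference and standard deviation, that 16 evaluable per group is the minimum for 80%, and that 17 enrolled with 10% dropout give about 78% on average. If a Mann-Whitney figure is quoted (about 74% to 75% at 15 per group), label it as conditional on normally distributed changes and on the literal rule in section 2.8.1.1.

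In section 2.5.3, print the denominator as 45+37-2.

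The cost is two small text edits and a slightly less favourable stated power, with no added enrolment. Should the sponsor prefer to keep an 80% claim after dropout, 16 / 0.9 = 17.8 means enrolling 18 per group, or 6 × 18 = 108 in total, which is 6 more than planned.

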### 2.6. Intervention

#### 2.6.1. Medical intervention

##### 2.6.1.1. CONS group

Depending on the patient’s condition, the doctor will select and perform one of the following 3 nerve block procedures: selective nerve root, medial branch, and epidural nerve blocks.

##### 2.6.1.2. DISCEC group

The surgeon will surgically decompress the nerve by removing the protruding intervertebral disc compressing the nerve root after excising the lumbar nerve root and partially resecting the lumbar lamina after incising the patient’s skin.

##### 2.6.1.3. FUSION group

Doctors use the interbody fusion method to surgically resolve spinal instability that may occur in the future when extensive posterior arch and facet joints are included during nerve decompression. The approach can be classified as anterior, lateral, and posterior fusion.

##### 2.6.1.4. Medication

•Intravenous infusion of amoburofen + normal saline 500 mL mix, flumarin 1000 mg bid.•Per oral administration of Paramacet 100 mg bid, neurontin 100 mg bid, Mulex Tab bid, and Stillen 2X Tab bid.

#### 2.6.2. Korean medical intervention

##### 2.6.2.1. Acupuncture treatment

A KM doctor will insert a needle into an acupuncture point suitable for back and lower extremity pain depending on the patient’s condition. The immersion time will be 15 minutes. To ensure safety, when performing acupuncture near the surgical site postoperatively, the presence or absence of a hematoma will be first confirmed through ultrasonography.

##### 2.6.2.2. Moxibustion treatment

A KM doctor will administer moxibustion treatment on acupuncture points suitable for back and lower extremity pain depending on the patient’s condition.

##### 2.6.2.3. Cupping therapy

A KM doctor will perform cupping therapy on acupuncture points suitable for back and lower extremity pain depending on the patient’s condition. The immersion time will be 5 minutes.

##### 2.6.2.4. Chuna treatment

A KM doctor will perform the Chuna technique for suitable patients with lumbar disc herniation according to the patient’s condition.

##### 2.6.2.5. Herbal medication

The conservative and surgical treatment groups will take Dokhwal Gisaeng-tang tid.

#### 2.6.3. Complementary and alternative medical intervention

##### 2.6.3.1. Diet therapy

Clinical nutritionists will check the patient’s underlying disease and current physical condition through consultation and prescribe a suitable diet.

